## 2.7 Participants' eligibility (Inclusion and exclusion criteria):

The pregnant women aged 15 – 49 years recruited in the CLIP Trial in both intervention and control clusters will be eligible to take part in the economic data collection (i.e., Form 1, Form 2 and Form 3) during the quarterly surveillance rounds. For qualitative assessments, only women who were identified at risk to a HDP in the pilot phase of the CLIP Trial, those willing to participate in 45-60 session will be eligible for participating in FGs. Likewise, husbands/father-in-law of those women (identified at risk to a HDP), those willing to participate in 45-60 session will be eligible for FGs. The CHCP handling the CLIP Trial package of intervention, the medical doctors at the referral health facilities where CLIP Trial participants are referred, and district health decision makers those willing to participate in 45-60 session will be eligible to participate in the FGs. Participants will be excluded, those who are not recruited in the primary CLIP Trial and or refuse to take part in the economics data collection procedures. The participants for qualitative assessments will be selected with the help of project staff, who are making home and health facility visits for CLIP Trial surveillance.

## 2.8 Plan of data analysis:

The total cost (quantities of resource utilized multiplied by their unit costs) will be calculated to estimate the cost on health system and family, and it will be denoted as an annual equivalent cost in US dollars rate of 2015. The incremental cost-effectiveness ratio (ICERs) will be calculated for maternal deaths/adverse pregnancy outcomes to compare the CLIP package of interventions and standard care from the societal perspective. The ICER represents additional cost of a more expensive but more effective intervention above that of the less expensive but less effective intervention divided by the difference in effectiveness. This estimate will allow us to compare the cost per unit maternal deaths/adverse pregnancy outcomes averted when switching from standard care to the CLIP package of interventions. Given the uncertainties involved in calculating the costs and trial outcomes, we will use simplistic sensitivity analysis to plot cost-effectiveness ratios. A key literature recommended using simple sensitivity analysis for CEA of package of interventions, because of the complexity of inherent correlations. The confidence region surrounding the cost-effectiveness ratio will be estimated using appropriate statistical methods, including bootstrap and Monte-Carlo analyses.

The qualitative data will be analyzed using QSR NVivo v10 software, and responses will be coded to form similar categories. Data will be interpreted through close communication between site investigators to ensure accuracy. Thematic analyses will be performed to

underscore additional cost drivers for cost modeling, implementation challenges, and perceptions of cost-benefits.

### **3. METHODS AND RESEARCH PLAN (INDIA)**

#### **Background and need for additional data collection in India**

The CLIP India Trial recruitment was completed as of October 2016; and data on health resource use was captured as part of Maternal and Newborn Health (MNH) data collection during the trial period. In addition, we have collected a wide range of maternal and newborn health services costs at 60 private health facilities; and six public health facilities. However, the data on patient level costs (i.e., out-of-pocket costs) are merely limited to health facility utilization.

*Study objective:* We aim to estimate societal costs, inclusive of opportunity costs as a result of HDPs- and other pregnancy- related illnesses and/or hospitalizations in order to complete CEA for the India CLIP trial in line with analysis completed in Pakistan and Mozambique, as described above.

*Design/settings:* A two-stage cluster rapid survey technique will be undertaken, using a population proportion to size sample in the study settings for definitive CLIP India Trial. This survey design has been widely used in expanded program on immunization (EPI) and endorsed by World Health Organization as 30X7 technique (i.e., 30 clusters; and 7 randomly selected households per cluster).

*Data collection:* A short-structured questionnaire will be administered to study eligible participants. The woman will be considered eligible, if she delivered (that resulted into a live and/or still birth(s)) during August to October 2016. Key variables will include, missed wage(s) by immediate care provider, missed wages by pregnant women; hired caretaker to do household chores; costs for meal procured during hospitalization, costs of anti-hypertensive medications at home, and transport cost (to and from health facility) related to HDPs and other pregnancy related illnesses-(other than HDPs). (Please refer to survey questionnaire)

A list of eligible households (i.e., pregnancies identified as HDP, and no-HDP in the intervention and control clusters) will be generated from MN-02 database for women who delivered during August to October 2016; and further stratified into women identified with HDPs and without HPDs. Later, we will group these eligible IDs into second-stage cluster(s) in respect to the geographical boundaries (i.e. distance of 1-2 kilometres between second-stage clusters); and randomly draw potential households for survey. A research assistant will administer the survey questionnaire. The total duration of face-to-face interview will be 15-20minutes/household.

Sample size: The CLIP cluster(s) serve as the primary-stage clusters, and Probability Proportion to Size (PPS) technique is applied to calculate number of second-stage clusters. Each cluster represents 7 households; and altogether 210 households will be needed to meet the desired sample size for this survey. Having added ~15% non-response rate to the sample size per cluster, we will have a total of 240 households (average 8 households per cluster). Out of 8 households in a given second-stage cluster, we will have a representative sample of 25% (~2 households/cluster) with HDPs; and 75% (~6 households/cluster) with no-HDPs. (Table 1)

Table 1: Desired sample size for household survey

| Cluster #    | # of preg. Recruited | # of clusters (PPS) | # of households (8 HH/Cluster) | HDP HH    | No HDP HH  |
|--------------|----------------------|---------------------|--------------------------------|-----------|------------|
| 3            | 987                  | 2                   | 16                             | 4         | 12         |
| 6            | 1291                 | 3                   | 21                             | 5         | 16         |
| 5            | 1371                 | 3                   | 22                             | 6         | 17         |
| 8            | 1111                 | 2                   | 18                             | 5         | 14         |
| 1            | 1266                 | 3                   | 21                             | 5         | 15         |
| 12           | 918                  | 2                   | 15                             | 4         | 11         |
| 2            | 1065                 | 2                   | 17                             | 4         | 13         |
| 4            | 1627                 | 3                   | 26                             | 7         | 20         |
| 7            | 1045                 | 2                   | 17                             | 4         | 13         |
| 10           | 1390                 | 3                   | 23                             | 6         | 17         |
| 9            | 1678                 | 3                   | 27                             | 7         | 20         |
| 11           | 1029                 | 2                   | 17                             | 4         | 13         |
| Total | 14778         | 30           | 240                     | 60 | 180 |

Ethics: Informed consent will be taken from participant(s) prior to administering survey questionnaire.

Data analysis:

Data analysis for the Indian CLIP trial CEA will be completed as described for both Mozambique and Pakistan in Section 2.8 above.

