| intervention clusters                                                           | 23.0%              | 11.1%              | 7.7%          | 4.3%                |
| Number of clusters (total)                                                      | 10                 | 12                 | 20            | 12                  |
| Number of births in Definitive CLIP Trial (2 years)                             | 22,400             | 24,405             | 18,000        | 13,000              |
| Additional births from Pilot CLIP Trial (4 clusters/1 year)                     | 4480               | n/a                | 1800          | 2400                |
| Total number of births (Pilot & Definitive Trials)                              | 26,880             | 24,405             | 19,800        | 19,200              |
| Expected referrals at month 6 of Pilot Trial assuming 5% incidence of HDP       | 112 [92, 132]      | 100 [81, 119]      | 45 [32, 58]   | 60 [45, 75]         |
| Number of women to be referred at month 6 of Pilot Trial to meet 50% use target | 56                 | 50                 | 23            | 30                  |
| Number of health facilities (total)                                             |                    |                    |               |                     |
| PHC/RHC                                                                         | 120                | 44                 | 42            | 22                  |
| EmOC                                                                            | 10                 | 10                 |               | 22                  |
| Number of CHCPs (total)                                                         | 250 CHEWs & 45 HAs | 170                | 400 LHWs      | 60 ANMs & 360 ASHAs |

ANM: assistant nurse midwife; AM: Administrative Posts; ASHA: accredited social health activist; CHEW: community health extension worker; CHCPs: community health care providers; CHW: community health worker; EmOC, emergency obstetric care; LGA: Local Government Area; LHW: Lady Health Worker; M&M: morbidity and mortality; MMR: maternal mortality ratio; PHC: Primary Health Centre; RHC, rural health centre.

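### The India household cost survey sets a 25:75 HDP quota and calls it representative, against the protocol's only HDP figure of 5% and with no stated step for recombining the two strata

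*Protocol*

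**What the plan says.** Appendix F section 3 of the protocol adds a household survey in India to supply patient-level costs that the trial's registry data do not cover: missed wages, hired help, meals, home medication and transport. On who is eligible it says: "The woman will be considered eligible, if she delivered (that resulted into a live and/or still birth(s)) during August to October 2016". The eligible women are listed from the MN-02 database for intervention and control clusters and "further stratified into women identified with HDPs and without HPDs".

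On size it says: "Each cluster represents 7 households; and altogether 210 households will be needed to meet the desired sample size for this survey". An allowance of about 15% for non-response raises this to 240, an average of 8 per second-stage cluster. For allocation across trial clusters, "Probability Proportion to Size (PPS) technique is applied to calculate number of second-stage clusters". Within each group of 8, "we will have a representative sample of 25% (~2 households/cluster) with HDPs; and 75% (~6 households/cluster) with no-HDPs". The sample-size table carries this through all 12 clusters to totals of 60 and 180.

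The analysis paragraph reads: "Data analysis for the Indian CLIP trial CEA will be completed as described for both Mozambique and Pakistan in Section 2.8 above". Section 2.8 of Appendix F multiplies resource quantities by unit costs, forms ICERs, and mentions simple sensitivity analysis, bootstrap and Monte Carlo methods. It mentions neither HDP strata nor sampling weights.

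The one HDP rate in the protocol is in Table 3 (section 2.11), in the row "Expected referrals at month 6 of Pilot Trial assuming 5% incidence of HDP".

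**The concern.** A sample with a fixed HDP share represents delivered women only if that share equals the share in the population. On the protocol's own 5% it does not. Taking more HDP households than their share is a sound way to gain precision on HDP costs, but an overall mean must then weight the strata back.

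The text points the analyst the other way. It calls the sample representative and hands the analysis to a section written for Pakistan and Mozambique, where resource use is collected through surveillance in all intervention and control clusters and no HDP quota exists.

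Two things are at stake. One is the level of India's family and opportunity costs, and so its comparability with the other two countries, which is the survey's stated aim. The other is incremental cost. The quota is the same in both arms, while the share of women identified with HDP may differ between them, because community providers in intervention clusters are trained to measure blood pressure and proteinuria (section 2.2) and those in control clusters are not (section 2.5).

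**Working it through.** **Inputs.** From Appendix F section 3: 30 second-stage clusters, 7 households each, about 15% non-response, a 25:75 quota, a three-month delivery window and 14,778 recruited pregnancies in 12 clusters. From Table 3: 5% HDP, and 1200 births per India cluster in two years. The ratio R of HDP to no-HDP cost is not in the documents; it is assumed to lie between 1 and 10.

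**1. The plan's own figures.** 30 × 7 = 210. 7 × 1.15 = 8.05, rounded to 8; 30 × 8 = 240. 0.25 × 240 = 60 and 0.75 × 240 = 180. Allocating 240 in proportion to recruited pregnancies gives every listed household count to within 1. In each row the HDP entry is a quarter of the households after rounding, so 25% is a uniform quota and not an observed cluster rate. (The rows sum to 61 and 181; this is rounding.)

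**2. Table 3 applies 5% to India.** Four pilot clusters × 300 births in six months = 1200; 1200 × 0.05 = 60, the India entry.

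**3. Size of the mismatch at 5%.** A proportional sample holds 0.05 × 240 = 12 HDP households. The quota takes 60, five times as many. Births in three months: 1200/24 × 3 × 12 = 1800, of which 90 with HDP and 1710 without. Sampling fractions are 60/90 = 67% and 180/1710 = 10.5%, a ratio of 6.33.

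**4. Effect on the mean surveyed cost if pooled unweighted.** With true HDP share p,

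pooled / true = (0.25R + 0.75) / (pR + 1 − p)

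| p | R = 1 | 1.5 | 2 | 3 | 5 | 10 |
|---|---|---|---|---|---|---|
| 5% | 1.00 | 1.10 | 1.19 | 1.36 | 1.67 | 2.24 |
| 10% | 1.00 | 1.07 | 1.14 | 1.25 | 1.43 | 1.71 |
| 15% | 1.00 | 1.05 | 1.09 | 1.15 | 1.25 | 1.38 |
| 20% | 1.00 | 1.02 | 1.04 | 1.07 | 1.11 | 1.16 |
| 25% | 1.00 | 1.00 | 1.00 | 1.00 | 1.00 | 1.00 |

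**5. Effect on total societal cost.** The survey supplies only part of the total. If surveyed items were 30% of the true total (assumption), the 36% at p = 5%, R = 3 becomes 0.30 × 36% = about 11%.

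**6. Effect on incremental cost.** A difference in HDP share between arms contributes (p1 − p0) × (HDP cost − no-HDP cost). With assumed costs of 3 and 1 and shares of 10% and 5%, this is 0.05 × 2 = 0.10. In the pooled quota sample it is (0.25 − 0.25) × 2 = 0. Separately, any arm difference in cost within the HDP stratum gets weight 0.25 instead of p, five times too much at 5%. The sign of the net error depends on the signs of these terms.

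**The case against.** The strongest reply is that nowhere does the protocol say the survey will be analysed unweighted. It is silent, and the method for recombining strata could sit in an analysis plan. The design also allows an approach in which no bias arises: because the frame is split by HDP status and the registry already holds resource use, stratum-specific costs could be applied to each arm's registry HDP count. A reader might infer that the plan commits to an unweighted analysis and that mean cost and the ICER are therefore biased; the documents do not support that.

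The reply is also right on three further points. The 5% is a uniform planning assumption for pilot referrals in all four countries, not an observed India rate; none is given, and if the true share were 25% the error in the overall mean would vanish. The survey covers only family and opportunity cost items, since unit costs were collected at 60 private and six public facilities and resource use comes from the registry. And the ICER rests on a difference between arms: the common mix cancels if HDP shares are equal by arm and the arm difference in cost is equal in both strata.

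None of this rescues the word representative, which the design does not earn on the only rate in the document. Nor is it mere missing detail, because the text describes the sample in a way that makes weighting look unnecessary. The between-arm point does not depend on 5%: even a true overall share of 25% leaves it open unless both arms are at 25%.

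**Conclusion.** The conflict in the text is firm: a uniform 25% HDP quota, with no basis given, is called representative in a protocol whose only HDP figure is 5%, under which 12 of 240 households would have HDP, not 60. The referral to section 2.8 leaves the recombination of strata unstated.

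The consequence is conditional. If the sample is pooled unweighted and true HDP is 5%, the mean of the surveyed items is overstated by 0% at equal costs, 19% at a cost ratio of 2, 36% at 3 and 67% at 5, and by less if true HDP is nearer 25%. Total societal cost is affected by less. The ICER could be biased in either direction; its size cannot be worked out from the documents. The point touches the economic evaluation only, not the primary outcome or safety.

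**What to change.** In Appendix F section 3, delete the word representative or give the source for 25%, and say that HDP households are deliberately oversampled. In the India analysis paragraph, add that each household is weighted by the inverse of its sampling fraction, by HDP stratum and arm, with stratum totals from the MN-02 list. Equivalently, combine the two stratum mean costs using each arm's observed HDP share. Standard errors or the bootstrap should respect both weights and clusters.

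Nothing changes in the field, since the totals come from the list used to draw the sample. The cost is slightly wider intervals. At 5% HDP, with equal cost variance in both strata, Kish's factor for weighting is 240 × (0.05²/60 + 0.95²/180) = 1.21, so standard errors rise by about 10% (√1.21 = 1.10).

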## **APPENDIX G:**

### **A policy analysis of postpartum maternal health policies in Ogun State, Nigeria**

#### **1. Background**

The WHO defines postpartum period as beginning immediately after childbirth and lasting a period of six weeks. This period is considered to be most critical for newborn and mothers, marking the most deaths for mothers and babies. However, this is the most neglected period for provision of critical care. In low income countries, an estimated 70% of women do not receive postpartum care. Further it is estimated that an estimated 15% develop potentially life-threatening problems. It is equally important to note that for every maternal death there are a large number of women who suffer illness and suffer long-term consequences of obstetric morbidity. From a purely clinical perspective, postpartum morbid consequences include problems such as postpartum infection, anaemia, perineal tears, urinary tract infection, and depression; others defined in the literature as long-term morbidities/disabilities include incontinence, fistula, pelvic inflammatory disease, genital prolapse, hypertension, haemorrhoids, nerve damage, pituitary failure, anaemia, and infertility.

Most of these deaths and morbidities are preventable, and a consequence of the poor health and nutritional status of the mother coupled with inadequate care before, during, and after delivery.

In a 2013 WHO systematic analysis of the causes of maternal deaths (in the years 2003–09), 480,000 or 19.7% maternal deaths worldwide occurred postpartum. In sub Saharan Africa alone, 15.2% maternal deaths occurred in the postpartum period, i.e. 42 days following delivery.

The WHO guidelines on the postnatal care for the mother and the newborn (2013) provide clinical recommendations for the care of the mother and baby upto six weeks after birth. Recommendations beyond the 24 hour period after birth include that the health care provider enquire about the general well-being and assess the woman's micturition and urinary incontinence, bowel function, healing of any perineal wound, headache, fatigue, back pain, perineal pain and perineal hygiene, breast pain, uterine tenderness and lochia. Further, the guidelines strongly suggest that women should be asked about emotional well-being as part of an assessment of overall well-being two to six weeks after birth.

Nigeria's maternal mortality contributes to 10% of the world's maternal death,. However, data from the 2005 National HIV/AIDS and Reproductive Health Survey indicates that only 41.2% of the women receive postnatal care and data from 2008 Nigeria Demographic and Health Survey in 2008 shows that only 32% of women received postnatal care within 42 days of delivery.

#### **2. Main aim**

The main aim of the project is to perform policy analysis to evaluate whether the national policies in the state of Ogun, Nigeria respond to the needs of postpartum women i.e. how they address any health condition attributed to and/or aggravated by pregnancy and childbirth that has a negative impact on the woman's wellbeing following childbirth.

#### **3. Objectives**

The policy analysis has the following objectives:

1. Review and compare the existing guidelines on postnatal care produced by Nigeria and International knowledge professional organizations-WHO (World Health Organisation), and national organisations such as the SOGON (Society of Obstetricians and Gynecologists of Nigeria)
2. Determine the current/recent postpartum needs in Nigeria by:
3. undertaking a literature review using papers published over the last five years (2009-2015) and using the data from the Demographic Health Survey (DHS) Nigeria to determine “needs” using the following proxies:
  - The burden of ill health postpartum in women in Nigeria by examining the prevalence and mortality rates in the postpartum period using the DHS (Demographic Health Survey) data
  - The service utilisation of postnatal care services in Nigeria
  - The service provision of postnatal care services in Nigeria
4. Identify gaps in national and local policies to address women’s needs for optimum postpartum care.
5. Interview stakeholders to triangulate findings from the literature and see what steps would be needed to address these gaps
6. Develop a set of evidence based policy recommendations for postpartum care for women in Ogun, Nigeria.

#### **4. Methods**

##### Review of guidelines

Buse Mays and Walt (2005) define ‘policy’ as a “broad statement of goals, objectives and means that create the framework for activity”. According to the WHO, ‘guidelines’ are systematically developed evidence-based statements which assist providers, recipients and other stakeholders to make informed decisions about appropriate health interventions (defined broadly to include not only clinical procedures but also public health actions).

In this project, both international guidelines and national policies to be analysed will be sought via literature reviews, agencies such public health institutions, professional societies, and via in-depth interviews and surveys with expert personnel, policy makers, health practitioners and patient-group representatives. The guidelines included would provide some recommendations to address postpartum maternal health.

